### Interventions

At the start of the study, each centre will be instructed in a brief presentation and practical training. When needed, a local research nurse is available during the inclusion period to advise the staff on use of the Foley catheter and/or oral misoprostol.

#### Induction with a transcervical Foley catheter

A 16 or 18 F Foley catheter will be introduced into the cervix and the balloon is filled with 30 cc of 0.9% NaCl or water. The Foley catheter can be placed digitally or using a speculum according to preference of the treating physician. No recommendations regarding disinfection will be given as there is no evidence for the best method. The external end of the Foley catheter will be tapped to the thigh without giving traction. Foley catheter location after placement can be evaluated digitally and/or by ultrasound. Women will be instructed to observe one hour of bed rest after every newly placed Foley catheter, while fetal condition and uterine activity will be monitored. Women will be examined every 12 hours if the transcervical Foley catheter does not detach spontaneously. When the Bishop score remains <6; the location of the Foley catheter will be evaluated and a new Foley catheter will be placed after 24 of 48 our depending on the preference of the participating centre.

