#### Induction with oral misoprostol

Patients in the misoprostol group will be treated according to the protocol used in the study of Gemund et al. [15]. Misoprostol will be administered every four hours with a maximum of three times a day for 4 days. For this study the protocol was adjusted to use of oral misoprostol. Women in the misoprostol group will receive 50 mcg misoprostol capsules. Since misoprostol 50 mcg tablets are not on the market and misoprostol as a raw material is not available, the 50 mcg tablets are made from the originally Cytotec 200 mcg, Searle, Maarsen, The Netherlands by the Leiden University Medical Centre pharmacy. 200 mcg Cytotec tablets are pulverized with a cube mixer. Capsules are prepared from portions of the powder mixture. Amount of powder mixture is optionally supplemented with microcrystalline cellulose to achieve volume for 100 capsules. Each capsule contains between 47.5 and 52.5 mcg misoprostol. High-performance liquid chromatography shows the standard retention time and sample are the same (within 2.5%). Women will be instructed to observe one hour of bed rest after every dose of misoprostol, while fetal condition and uterine activity will be monitored. When there will be 3 or more contractions in 10 minutes while the Bishop score is still <6 or when the fetal heart rate is not reassuring the next misoprostol dose will be withheld. Amniotomy and oxytocin infusion can be started at any moment of the day when the Bishop score is ≥ 6, and at least 4 hours after the last dose of misoprostol. Women will be treated for a maximum of 4 days with Foley catheter or oral misoprostol. If after 4 days the cervix remains unfavorable, the induction is considered to be failed and further management will be decided individually by the treating physician. The number of women needing more than 48 hours of induction is expected to be very low.

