### Outcome measures

The primary endpoint will be a composite outcome of neonatal asphyxia (defined as a neonatal pH ≤ 7.05 and/or 5 minute Apgar score <7) and/or post partum haemorrhage (defined as an estimated blood loss of ≥1000 cc ascertained over 24 h post partum). We have chosen this combined outcome as both conditions are thought to be a result of hyperstimulation.

Secondary endpoints:

• Mode of delivery (Caesarean section, vaginal operative delivery, spontaneous delivery) and the reason for operative delivery, i.e. suspected fetal distress and/or failure to progress.

• Induction to delivery time,

• Use of analgetics

• Oxytocin use

• Number of misoprostol gifts/Foley catheters used.

• Number of vaginal examinations

• Maternal morbidity

 ○ Post partum blood transfusion and number of packed cells

 ○ Tachysystole (defined as more than five contractions in ten minutes over a minimal period of two times ten minutes)

 ○ Hyperstimulation (defined as tachysystole with FHR changes (defined as a non reassuring CTG by treating physician))

 ○ Uterine hypertonus (defined as a contraction lasting longer than two minutes with FHR changes)

 ○ Uterine rupture (occurrence of clinical symptoms (abdominal pain, abnormal fetal heart rate pattern, acute loss of contractions, vaginal blood loss) leading to an emergency caesarean delivery, at which the presumed diagnosis of uterine rupture was confirmed; or peripartum hysterectomy or laparotomy for uterine rupture after vaginal birth)

 ○ Uterine scar dehiscence (separation of a pre-existing scar that does not disrupt the uterine serosa as seen during caesarean section, without clinical consequences)

 ○ Maternal infection during labour (defined as fever, i.e. temperature ≥ 37.8°C, or fetal tachycardia AND start of antibiotics)

 ○ Maternal infection within one week post partum (defined as fever, i.e. temperature ≥ 37.8°C, AND start of antibiotics)

 ○ Start of intravenous antibiotics

 ○ Endo(myo)metritis or urinary tract infection within one week post partum (proven positive vaginal/urine culture)

 ○ Other medication used during labour such as tocolytics.

• Neonatal parameters consisting of:

 ○ Fetal tachycardia (sustained fetal heart rate above 160 beats per minute)

 ○ Gender

 ○ Weight at birth

 ○ Meconium-stained liquor

 ○ Apgar scores <7 at 1 minute

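### During ripening, scheduled uterine and fetal monitoring depends on the allocated arm (per misoprostol dose or per new Foley catheter), so tachysystole, hyperstimulation, hypertonus and fetal tachycardia are open to unequal ascertainment

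*Protocol article*

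**What the plan says.** The Interventions section attaches fetal and uterine monitoring to the procedure itself.

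- **Foley arm** (Induction with a transcervical Foley catheter): "one hour of bed rest after every newly placed Foley catheter, while fetal condition and uterine activity will be monitored". If the cervix stays unfavourable, "a new Foley catheter will be placed after 24 of 48 our depending on the preference of the participating centre" (read here as 24 or 48 hours). Between placements the text gives only this: "Women will be examined every 12 hours if the transcervical Foley catheter does not detach spontaneously". CTG is not mentioned for that check.
- **Misoprostol arm** (Induction with oral misoprostol): "one hour of bed rest after every dose of misoprostol, while fetal condition and uterine activity will be monitored". On frequency: "Misoprostol will be administered every four hours with a maximum of three times a day for 4 days". Three a day is a ceiling. The next dose is held back when contractions reach a set frequency while the cervix is still unfavourable, and "when the fetal heart rate is not reassuring the next misoprostol dose will be withheld".
- **Duration**: both methods stop at 4 days, but "The number of women needing more than 48 hours of induction is expected to be very low".

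Outcome measures lists four secondary endpoints that rest on contraction or heart-rate recording: "Tachysystole (defined as more than five contractions in ten minutes over a minimal period of two times ten minutes"), hyperstimulation (tachysystole with a CTG that the treating physician judges non-reassuring), uterine hypertonus and sustained fetal tachycardia. None of them is given an observation period. In the same list, blood loss is counted over 24 hours and post-partum infection over one week. The trial is open-label.

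**The concern.** These four events are reliably recorded only while contractions and fetal heart rate are being watched. In ripening, the plan sets the amount of scheduled watching by allocation: a woman on repeated doses has several monitored hours, each straight after a dose, while a woman with one catheter in place has one. The rule for withholding a dose also requires contractions and heart rate to be assessed in the misoprostol arm, and the Foley text has no counterpart.

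More looking finds more events. The Background expects less hyperstimulation with Foley, and Outcome measures justifies the primary composite on the ground that both of its components are thought to follow from hyperstimulation. Unequal ascertainment would push these secondary results in the expected direction even if true rates were equal, and so could appear to confirm the trial's mechanism. If monitored time is not captured during the trial, it cannot be reliably reconstructed afterwards.

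**Working it through.** The article states no figure for monitored time, so there is none to reproduce. The schedule can be counted.

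**Inputs.** Misoprostol: 1 h per dose, doses at 0, 4 and 8 h of each day, at most 3 a day for at most 4 days. Foley: 1 h per catheter, one catheter per 24 h or per 48 h. All are from the two Interventions subsections.

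**Step 1: scheduled ripening-phase hours at full dosing.** Ratio = doses × 1 h ÷ catheters × 1 h.

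| Ripening lasts | Misoprostol (h) | Foley, 24-h replacement (h) | Ratio | Foley, 48-h replacement (h) | Ratio |
|---|---|---|---|---|---|
| 4 h | 1 | 1 | 1 | 1 | 1 |
| 8 h | 2 | 1 | 2 | 1 | 2 |
| 12 to 24 h | 3 | 1 | 3 | 1 | 3 |
| 48 h | 6 | 2 | 3 | 1 | 6 |
| 72 h | 9 | 3 | 3 | 2 | 4.5 |
| 96 h | 12 | 4 | 3 | 2 | 6 |

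The ratio is 3 for one full dosing day. It reaches 6 only in centres that replace at 48 h, when ripening runs into a second day with full dosing. Withheld doses lower it. So does a catheter that has to be placed again.

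**Step 2: dilution by monitoring in labour.** The article does not describe monitoring after amniotomy, during oxytocin or in labour. Assume L hours, equal in both arms. Then ratio = (misoprostol hours + L) ÷ (Foley hours + L).

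- One full dosing day, 3 h against 1 h: L = 4 gives 7/5 = 1.40; L = 8 gives 11/9 = 1.22.
- 48 h with 48-h replacement, 6 h against 1 h: L = 4 gives 10/5 = 2.00; L = 8 gives 14/9 = 1.56.

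**Step 3: what this could do to a risk ratio.** Assume the same 1% chance of detecting an event per monitored hour in both arms (an assumption; the article gives no rate) and the planned 930 women per arm. Risk = 1 − 0.99^hours. The z values use the pooled two-proportion test.

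| Scenario | Misoprostol | Foley | Risk ratio | z | p |
|---|---|---|---|---|---|
| 3 doses v 1 catheter, ripening only | 1 − 0.99^3 = 2.97% | 1.00% | 2.97 | 3.05 | 0.002 |
| 2 doses v 1 catheter, ripening only | 1 − 0.99^2 = 1.99% | 1.00% | 1.99 | 1.76 | 0.08 |
| 3 v 1, plus L = 4 | 1 − 0.99^7 = 6.8% | 1 − 0.99^5 = 4.9% | 1.39 | 1.7 | 0.08 |
| 3 v 1, plus L = 8 | 1 − 0.99^11 = 10.5% | 1 − 0.99^9 = 8.6% | 1.21 | 1.3 | 0.18 |

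With no true difference, the risk ratio lies above 1 in every row. Its size depends heavily on how much monitoring the arms share.

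**The case against.** A reader might infer that these endpoints are looked for 3 to 6 times as long with misoprostol over the whole induction. The documents do not support that. The figure covers scheduled ripening hours at the dosing ceiling. The endpoints are not confined to ripening, and monitoring in labour is not described for either arm, so total observation time cannot be derived. The 12 h against 2 h contrast also belongs to the 4-day maximum, while the article expects few women to go beyond 48 hours. All of this stands.

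Four further points deserve an answer.

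- **The article is condensed.** Observation windows and case-record fields may sit in the full protocol, and their absence here is not the finding. The finding is the unequal schedule, which is stated, set against endpoints that depend on it.
- **More doses mean more real exposure.** Some extra events after repeated dosing would be true effects of the regimen, and whole-induction incidence is the natural intention-to-treat summary. This stands. It rules out making the first monitored hour the main comparison, because that hour covers one of up to twelve doses.
- **The consequences are limited.** The primary composite uses cord pH, 5-minute Apgar and blood loss, none of which comes from these hours. The safety topics named for the interim analyses are infection, asphyxia and haemorrhage. A knock-on to maternal infection during labour through fetal tachycardia is weak, since that endpoint concerns labour and also requires antibiotics to be started.
- **Part of the information is already collected.** Numbers of doses and catheters are a listed secondary endpoint, so scheduled ripening time can be approximated for each woman. This lowers the cost of the fix. It does not show when an event occurred.

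**Conclusion.** The concern holds for scheduled monitoring during ripening. Following the plan as written, that monitoring is up to 3 times as long with misoprostol (24-hour replacement) or up to 6 times (48-hour replacement, ripening into a second day), and 1 to 2 times as long when only one or two doses are given. Tachysystole, hyperstimulation, hypertonus and fetal tachycardia are therefore exposed to ascertainment that would tend to favour Foley.

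The effect on the reported results cannot be fixed from the article. Under the assumed 1% per monitored hour and one full dosing day, the spurious risk ratio is about 3 if ripening is the only observation, about 1.4 with 4 shared labour hours, and about 1.2 with 8. The direction is clear; the size is not.

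The primary composite is not directly affected. This is a worthwhile, inexpensive improvement to secondary endpoints that carry the trial's mechanistic argument. It does not challenge the main comparison.

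**What to change.** 1. Keep whole-induction incidence, by intention-to-treat, as the main summary for these four endpoints.
2. Record in the eCRF the phase in which each event occurred: ripening, or from amniotomy, oxytocin or active labour to delivery.
3. Record CTG start and stop times. Failing that, approximate monitored ripening time from the numbers of doses and catheters already collected, at one hour each.
4. Report the four endpoints separately by phase and, as a sensitivity analysis, per monitored hour.
5. Do not make the first monitored hour the main comparison.

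The cost is a few extra eCRF fields and a wording change to the endpoint definitions. Intervals within each phase will be wider. The hourly rate partly divides out real repeated exposure, so it should be read as supportive only. Clinical monitoring stays as it is.

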#### Induction with oral misoprostol

Patients in the misoprostol group will be treated according to the protocol used in the study of Gemund et al. [15]. Misoprostol will be administered every four hours with a maximum of three times a day for 4 days. For this study the protocol was adjusted to use of oral misoprostol. Women in the misoprostol group will receive 50 mcg misoprostol capsules. Since misoprostol 50 mcg tablets are not on the market and misoprostol as a raw material is not available, the 50 mcg tablets are made from the originally Cytotec 200 mcg, Searle, Maarsen, The Netherlands by the Leiden University Medical Centre pharmacy. 200 mcg Cytotec tablets are pulverized with a cube mixer. Capsules are prepared from portions of the powder mixture. Amount of powder mixture is optionally supplemented with microcrystalline cellulose to achieve volume for 100 capsules. Each capsule contains between 47.5 and 52.5 mcg misoprostol. High-performance liquid chromatography shows the standard retention time and sample are the same (within 2.5%). Women will be instructed to observe one hour of bed rest after every dose of misoprostol, while fetal condition and uterine activity will be monitored. When there will be 3 or more contractions in 10 minutes while the Bishop score is still <6 or when the fetal heart rate is not reassuring the next misoprostol dose will be withheld. Amniotomy and oxytocin infusion can be started at any moment of the day when the Bishop score is ≥ 6, and at least 4 hours after the last dose of misoprostol. Women will be treated for a maximum of 4 days with Foley catheter or oral misoprostol. If after 4 days the cervix remains unfavorable, the induction is considered to be failed and further management will be decided individually by the treating physician. The number of women needing more than 48 hours of induction is expected to be very low.

### Outcome measures

The primary endpoint will be a composite outcome of neonatal asphyxia (defined as a neonatal pH ≤ 7.05 and/or 5 minute Apgar score <7) and/or post partum haemorrhage (defined as an estimated blood loss of ≥1000 cc ascertained over 24 h post partum). We have chosen this combined outcome as both conditions are thought to be a result of hyperstimulation.

Secondary endpoints:

• Mode of delivery (Caesarean section, vaginal operative delivery, spontaneous delivery) and the reason for operative delivery, i.e. suspected fetal distress and/or failure to progress.

• Induction to delivery time,

• Use of analgetics

• Oxytocin use

• Number of misoprostol gifts/Foley catheters used.

• Number of vaginal examinations

• Maternal morbidity

 ○ Post partum blood transfusion and number of packed cells

 ○ Tachysystole (defined as more than five contractions in ten minutes over a minimal period of two times ten minutes)

 ○ Hyperstimulation (defined as tachysystole with FHR changes (defined as a non reassuring CTG by treating physician))

 ○ Uterine hypertonus (defined as a contraction lasting longer than two minutes with FHR changes)

 ○ Uterine rupture (occurrence of clinical symptoms (abdominal pain, abnormal fetal heart rate pattern, acute loss of contractions, vaginal blood loss) leading to an emergency caesarean delivery, at which the presumed diagnosis of uterine rupture was confirmed; or peripartum hysterectomy or laparotomy for uterine rupture after vaginal birth)

 ○ Uterine scar dehiscence (separation of a pre-existing scar that does not disrupt the uterine serosa as seen during caesarean section, without clinical consequences)

 ○ Maternal infection during labour (defined as fever, i.e. temperature ≥ 37.8°C, or fetal tachycardia AND start of antibiotics)

 ○ Maternal infection within one week post partum (defined as fever, i.e. temperature ≥ 37.8°C, AND start of antibiotics)

 ○ Start of intravenous antibiotics

 ○ Endo(myo)metritis or urinary tract infection within one week post partum (proven positive vaginal/urine culture)

 ○ Other medication used during labour such as tocolytics.

• Neonatal parameters consisting of:

 ○ Fetal tachycardia (sustained fetal heart rate above 160 beats per minute)

 ○ Gender

 ○ Weight at birth

 ○ Meconium-stained liquor

 ○ Apgar scores <7 at 1 minute

 ○ Admission to the neonatal ward/NICU and its reason (suspected infection, infection proven by positive culture, other reason admission to medium or intensive care).

An economic analysis will be conducted alongside the PROBAAT-II trial. In order to do so, resource use in different phases of delivery will be collected in the electronic case-record form (eCRF). To our knowledge, no validated questionnaires on women’s preference of induction of labour method are available. Therefore women’s preference for the method of induction will be evaluated by a post partum questionnaire developed for this study, based on a validated questionnaire by Wijma et al. This questionnaire was developed to assess women’s experience of labour [16].

### Follow up of women and infants

Details of admission of women and newborns will be recorded as will maternal and neonatal complications. Long term follow-up is not part of the current study.

### Analysis

This trial is designed as a non-inferiority trial. Primary analysis will be by intention-to-treat. In a comparative trial, where the aim is to decide if two treatments will be different, an intention-to-treat analysis is generally conservative: the inclusion of protocol violators and withdrawals will usually make the results from the two treatment groups more similar. However, for a non inferiority trial this effect is no longer conservative: any blurring of the difference between the treatment groups will increase the chance of declaring non inferiority [17]. We will therefore also perform a per protocol analysis. Relative risks and 95% confidence intervals will be calculated for the relevant outcome measures. We will additionally adjust for the stratified randomization when calculating the relative risk. Differences between categorical variables will be tested with the Chi-square test, or if the expected cell count is below 5 with the Fisher’s exact test. Non-normally distributed continuous variables will be tested with the Mann–Whitney *U* test. Time to delivery will be assessed using Kaplan-Meier analysis. For the economic analysis we plan a cost-minimisation procedure, as we designed a non-inferior trial and expect no differences in outcomes. Resource uses are multiplied by their specific costs, which are estimated according to recent guidelines on costing health care services. When a relevant differences in outcomes will be observed, we will perform a cost-effectiveness analysis, in which we calculate the additional cost per prevented case of fluxus or asphyxia and the cost per prevented Caesarean section. Mean resource use and costs are compared between both arms, if any difference of interest in primary and/or secondary outcomes occurs a cost-effectiveness analysis will be performed. Using an interaction term we will assess whether the difference in effect between misoprostol and Foley catheter is consisted in nulliparous and multiparous women.

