### Procedures, recruitment, randomisation, collection of baseline data

This trial will be a multicentre, open-label, randomised controlled trial. The study will be performed within the Dutch Consortium for Studies in Women’s Health and Reproductivity (http://www.studies-obsgyn.nl). Participating hospitals can be district, teaching or academic hospitals. Before entry into the study, women will be informed about the aims, methods, reasonably anticipated benefits and potential hazards of the study. This will generally be at least 1 day before actual admission for induction. They will be informed that their participation is voluntary and that they may withdraw consent for participation at any time during the study. Choosing not to participate will not affect care. In each centre an independent physician will be available for more detailed information for both patients and colleagues if desired. After counselling, written informed consent will be obtained. The consent form must be signed before performing of any study-related activity. Randomisation will be performed web-based using ALEA. After entering patient initials, confirming inclusion criteria and absence of exclusion criteria, randomisation will be performed realtime based on an algorithm. We will use fixed block sizes of 2 and 4 and stratify for centre and parity. As there is no prespecified randomisation list, it will be hardly possible for anyone to know the next allocation. Randomisation will take place after evaluation of the fetal condition by CTG, just before start of induction. Eligible women will be allocated in a 1:1 ratio to induction with a Foley catheter or oral misoprostol. There will be no blinding of patients and caregivers, as this is not feasible with these two treatment methods. Baseline demographic, obstetric and medical histories, and details of delivery and health care received till the time of discharge will be recorded for all women. Data will be entered into an electronic case-record form (Oracle Clinicle version 4.5.3) accessible through our study website with a personal login http://www.studies-obsgyn.nl/probaat2. All changes made in this electronic case-record form will be captured in an audit trial. In Oracle Clinicle checks will be programmed to identify errors. All electronic case-record forms will be checked for consistency and to correct errors.

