### Sample size

To calculate an adequate sample size we searched the literature for comparisons between oral misoprostol and Foley catheter. There is only one study which directly compared induction of labour with oral misoprostol and Foley catheter. This study does not report on our primary outcome measures which makes it insufficient to use for our power calculation [10]. A few studies reported on a comparison of vaginal misoprostol and prostaglandin E2, but different dosages were used and from the reported outcome parameters it was not possible to calculate the composite outcome we use [6]. Therefore we used data from the PROBAAT trial, comparing prostaglandin E2 (prostin) with Foley catheter [9]. In the Probaat trial the incidence of the composite outcome of pH ≤ 7.05 and/or an Apgar < 7 at 5 minutes (at least one known) and/or haemorrhage ≥1000 cc post partum was 12.7% when a Foley catheter was used and 16.4% when Prostaglandin E2 gel was used. We expect the incidence of the composite outcome to be lower when using oral misoprostol than when using prostaglandin E2 but slightly higher than when a Foley catheter is used [5]. We expect that about 25% of umbilical cord pH’s will be missing, while the 5 minute Apgar will be complete in nearly all cases. So, if the umbilical artery pH data will be missing, neonatal outcome will be classified as abnormal if the 5 minute Apgar will be <7 and as normal if the Apgar was ≥ 7. With a power of 80% (1-β) and a one-sided 0.05 risk of type I error (α), we need 1860 participants (930 per group) to demonstrate non-inferiority, i.e. that the absolute difference in the composite outcome will be less than 5% in the misoprostol group compared to the Foley catheter group, when assuming that the composite outcome was 12.7% in the Foley catheter group and 13.7% in the misoprostol group and an 5% exclusion rate from the per protocol analysis. This sample size will also give us more than 80% power to demonstrate non-inferiority, i.e. less than 5% increase in the proportion of caesarean sections when using misoprostol compared to Foley catheter, assuming 23% caesarean sections in both groups [9]. We used NQuery Advisor 7.0, with the two group test of equivalence in proportion (NQueryAdvisor; Machin 1987) to calculate the sample size.

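### Non-inferiority is defined as an absolute difference below 5 points, but the article describes only relative risks and tests of no difference, which cannot decide it

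*Protocol article*

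**What the plan says.** The Sample size section of the protocol article defines non-inferiority as "that the absolute difference in the composite outcome will be less than 5% in the misoprostol group compared to the Foley catheter group". It uses a one-sided alpha of 0.05 and 80% power. A second non-inferiority aim, also with a 5% limit, is stated for caesarean section.

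The Analysis section declares a non-inferiority design, makes intention-to-treat primary and adds a per-protocol analysis. Its methods for binary outcomes are:

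- as the estimate, "Relative risks and 95% confidence intervals will be calculated for the relevant outcome measures";
- a further version of that same ratio, corrected for the factors used to stratify allocation;
- chi-square tests, or Fisher's exact test where expected counts are small;
- an interaction term for parity.

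The article does not give a confidence interval for a risk difference, or a rule comparing such an interval with the margin. The interim rule under Monitoring is also based on a difference (P < 0.001).

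On direction, the Abstract presents the Foley catheter as the method to be shown non-inferior to misoprostol. The Sample size section tests misoprostol against Foley.

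**The concern.** The margin and the planned estimate are on different scales. A limit on a risk difference becomes a limit on a ratio only once a reference rate is fixed, and the observed Foley rate need not equal the assumed 12.7%. That figure comes from one earlier trial with a different prostaglandin comparator. The Sample size section itself says that the only direct comparison of oral misoprostol with Foley did not report this outcome.

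A chi-square or Fisher test addresses a null of no difference, so failing to reject it says nothing about a 5-point margin.

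If the article is followed as written, the primary estimate and the primary hypothesis do not meet. The scale, the confidence level and the adjustment behind the non-inferiority claim could then be chosen after the data are seen, in an open-label trial.

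**Working it through.** **Inputs.** From Sample size: margin 0.05 (absolute), one-sided alpha 0.05, power 0.80, rates 0.127 (Foley) and 0.137 (misoprostol), "an 5% exclusion rate from the per protocol analysis", 930 per group. From Procedures: 1:1 allocation. From Analysis: 95% intervals.

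**1. Which scale the design is on.** Unpooled normal approximation for a risk difference:

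n = [p₁(1−p₁) + p₂(1−p₂)] (z₀.₉₅ + z₀.₈₀)² / (margin − expected difference)²

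- Variance sum: 0.127×0.873 + 0.137×0.863 = 0.1109 + 0.1182 = 0.2291
- (1.645 + 0.842)² = 6.183
- Distance to margin: 0.05 − 0.01 = 0.04
- n = 0.2291 × 6.183 / 0.0016 = 885.3, so 886 per group and 1772 in total; 1772/0.95 gives 1866

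The stated 1860 is reproduced to within rounding, so the trial is sized on the absolute difference, misoprostol against Foley. In the Abstract's direction the distance is 0.05 + 0.01 = 0.06, which gives 394 per group and 830 in total after exclusions. That does not match 1860.

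**2. What 5 points means as a ratio.** RR = (p + 0.05)/p, with p the Foley rate:

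| Foley rate | RR equal to +5 points |
|---|---|
| 8% | 1.63 |
| 12.7% | 1.39 |
| 18% | 1.28 |

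**3. Whether the two scales can disagree.** The examples are hypothetical, with 930 per arm, Wald limits, and RR 1.39 (the ratio at the assumed Foley rate) as an illustrative bound:

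| Foley v misoprostol | Level | Upper RD (points) | Upper RR | Against 5 points / against 1.39 |
|---|---|---|---|---|
| 12.7% v 13.7% | 90% | 3.6 | 1.31 | pass / pass |
| 12.7% v 13.7% | 95% | 4.1 | 1.36 | pass / pass |
| 8% v 9% | 90% | 3.1 | 1.45 | pass / fail |
| 8% v 9% | 95% | 3.5 | 1.52 | pass / fail |
| 18% v 21% | 90% | 6.0 | 1.36 | fail / pass |
| 18% v 21% | 95% | 6.6 | 1.40 | fail / fail |
| 186 v 201 events | 90% | 4.7 | 1.25 | pass / pass |
| 186 v 201 events | 95% | 5.3 | 1.29 | fail / pass |

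At the design rates the scales agree. Away from them they can disagree in either direction, and some disagreements depend on the confidence level.

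**4. The test of no difference.** At 12.7% v 13.7% with 930 per group, a two-sided 0.05 test has power of about 9 to 10%. A non-significant result is the expected outcome and is not evidence of non-inferiority.

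**5. The confidence level.** Power = Φ(0.04/SE − z), with SE = √(0.2291/n):

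| n per group | SE | One-sided 0.05 (90% CI) | One-sided 0.025 (95% CI) |
|---|---|---|---|
| 930 | 0.01570 | 81.7% | 72.2% |
| 883.5 (after 5% exclusions) | 0.01610 | 79.9% | 70.0% |

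For 80% power read from a 95% interval, n is 1124 per group, or 2368 in total after exclusions.

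**6. Caesarean section.** At 23% in both groups with a 5-point margin and one-sided 0.05, n is 876 per group and power is 82.0% at 930. This agrees with the article's claim of more than 80%. Read from a 95% interval, power at 930 is 72.6%.

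**The case against.** The best defence is that the Sample size section already fixes outcome, scale, margin and alpha, and the Analysis section names both analysis sets and explains why. A risk difference comes from the same two-by-two table as the relative risk. The article is condensed, and a full protocol or analysis plan could hold the interval method and decision rule. All of this is fair, and it limits what can be claimed:

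- A reader might infer that no analysis planned anywhere tests the hypothesis. The documents do not support that; only this article is at hand.
- A reader might infer that chi-square is the primary test. The article never says so: that sentence is about categorical variables in general, and the relative-risk sentence is about outcome measures in general.
- A reader might infer that the margin will be converted to RR 1.39. The article makes no such conversion; 1.39 is used above only as an illustration.
- The absolute scale is not wholly absent from the Analysis section. The conditional cost per prevented case needs an absolute difference, although it is not a margin test.
- The 18% v 21% disagreement exists at 90% and disappears at the 95% level that the article names.

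What remains is more than an omitted detail. The article does not leave the scale of estimation open: it names the relative risk, and places the stratified adjustment on that scale too. That does not fit its own absolute margin.

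**Conclusion.** The point holds for the analysis as described in this article. The absolute margin of 5 points, for the composite and for caesarean section, is not matched by any described estimate or decision rule, and relative risks with tests of no difference cannot supply one. The sample size is not at fault: 1866 against the stated 1860.

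The practical size has two parts. First, the ratio equivalent of the margin runs from 1.63 to 1.28 over Foley rates of 8% to 18%, so the verdict can depend on the scale once the rate moves away from 12.7%. Second, the unresolved confidence level is worth about 10 percentage points of power on the composite.

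These figures assume Wald limits, unadjusted analyses and the article's event rates. The 8% and 18% rates are illustrations, not forecasts.

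**What to change.** 1. Reconcile the direction first. The Abstract (Foley non-inferior to misoprostol) and the Sample size section (misoprostol against Foley) must agree before any bound is set. The 1860 corresponds to the second.
2. Name the risk difference, adjusted for the stratification factors centre and parity (for example Mantel-Haenszel), as the primary estimate. If the Sample size direction is kept, this is misoprostol minus Foley.
3. State the rule: non-inferiority is concluded if the upper confidence limit lies below 5 points, examined in both the intention-to-treat and per-protocol sets. Apply the same method to caesarean section.
4. State the confidence level. A two-sided 90% interval matches the one-sided 0.05 behind 1860. If the 95% interval is used for the decision, restate the power as about 72% (70% after 5% exclusions), or enlarge the trial to about 2368.
5. Keep the relative risk as a supporting estimate, and say that the chi-square and Fisher tests do not bear on the non-inferiority conclusion.

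With the 90% interval and the Sample size direction, this costs wording only and leaves the sample size unchanged. If a full protocol or analysis plan already contains such a rule, the article's Analysis section need only be aligned with it.
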